##### Participant selection

Leaders and counselors will be actively recruited, and patient records will be extracted from the electronic medical record. The Phase 1 eligibility criteria will be used to determine eligibility of counselors and leaders (see Phase 1. Participants). Patient records will be included in data extractions if the patients were receiving methadone or buprenorphine along with group counseling; and were inducted on medication for opioid use disorder within 6 months of MBC integration. We anticipate that the demographics of the Phase 2 participants will be similar to those in Phase 1.

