##### Measures

All effectiveness and implementation outcome data collected in Phase 2 will be fully deidentified data extracted from the medical record. Counselor data will only be extracted for those who completed the MBC workshop, whereas patient data will only be extracted for those treated by counselors who completed the workshop. Patient treatment engagement data and opioid abstinence will be collected monthly across 6 months prior to and post MBC integration to evaluate preliminary effectiveness and implementation. Counselor MBC exposure and fidelity will be assessed post MBC integration only. Demographic data will also be extracted for all counselors and patients (e.g. age, biological sex, race, ethnicity). Finally, information about prior treatment at the OTP (i.e. patients who received care previously but came in again as new patients), patient MOUD type and dose, and patient DSM diagnoses (including other substance use or mental health disorders) will be extracted.

Patient treatment engagement: The primary MBC effectiveness outcome measure is patient treatment engagement, which we have broadly defined to encompass both completion of methadone/buprenorphine dosing visits and attendance at counseling/psychosocial intervention appointments. Approximately 20 charts per site (*N* = 80) will be randomly selected from new patients that entered treatment over the 6 months prior to MBC integration. An additional separate set of 20 new patient charts per site (*N* = 80) will be extracted to evaluate treatment engagement in the 6 months following integration. Charts will be reviewed to identify the proportion of treatment visits attended (i.e. MOUD dosing visits and individual/group counseling appointments) out of total visits scheduled for each patient, as well as the total number of weeks each patient was retained in treatment.

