Patient opioid abstinence: The secondary MBC effectiveness outcome measure is patient opioid abstinence. The same charts extracted for treatment engagement will also be reviewed for opioid abstinence. Charts will be reviewed to identify the proportion of negative opioid urine screens for each patient monthly across 6 months prior to and post MBC integration. We anticipate that some patients in our chart sample will discontinue treatment (e.g. due to discharge or leaving the OTP) during the 6 months prior to and post MBC integration. For patients who discontinue treatment, opioid abstinence will be calculated as the proportion of negative urine screens for each month that they were present in the program. We will include an indicator in the data set to denote that urine drug screen data was unavailable for the months following patient treatment discontinuation.

Counselor MBC exposure: The primary MBC implementation outcome measure is monthly counselor MBC exposure. Counselor-level exposure refers to the number of group counseling sessions each month where MBC was administered divided by the total number of group sessions completed each month by OTP counselors (i.e. total opportunities to use MBC) [62]. The total number and dates of monthly completed group counseling sessions delivered by counselors who attended the MBC workshop. will be extracted from the EMR at all four sites. Documentation from each of these counseling sessions will be reviewed to determine whether or not MBC was recorded. Monthly MBC exposure values will be computed by dividing the total number of sessions with MBC documentation by the total number of sessions completed across each of the 6 months post MBC integration.

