##### MBC effectiveness and implementation outcome data analysis

Descriptive statistics will be explored (means, standard deviations, ranges) for all outcome variables to determine preliminary MBC effectiveness and implementation across all sites. Mean comparisons will test MBC effectiveness and implementation hypotheses. Specifically, *t*-tests will be conducted to compare average pre- and post-MBC treatment engagement proportions/number of weeks of MOUD and counseling attended and opioid abstinence proportions.

Additional exploratory analyses will employ Multi-Level Modeling to identify the impact of MBC fidelity on patient treatment engagement/abstinence as well as predictors of MBC exposure and fidelity at both the individual counselor and OTP level while accounting for data nested within OTPs. Predictors of patient treatment engagement/abstinence to be explored include biological sex, gender identity, age, race, ethnicity, prior MOUD receipt at the OTP, MOUD type and dose, and number of co-occurring disorders. Predictors of MBC exposure and fidelity to be explored at the counselor level include biological sex, gender identity, age, race, ethnicity, years employed at the OTP, and attitudes toward MBC. Predictors to be explored at the OTP level include organizational functioning and implementation climate (measured in Phase 1; see Phase 1 Quantitative Surveys). Missing data will be analyzed to evaluate percent missingness, and analyses will employ multiple imputation methods in the event of substantial missing data.

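### Weeks retained is capped by each patient's entry date because entry and follow-up share one 6-month calendar window, yet it is compared as a raw mean by t-test

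*Protocol article*

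**What the plan says.** All of this is in Phase 2 of the protocol article.

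- **Sampling of pre charts (Measures, patient treatment engagement).** About 20 charts per site, 80 in all, "will be randomly selected from new patients that entered treatment over the 6 months prior to MBC integration".
- **Post charts (same paragraph).** A separate set of 80 new-patient charts "will be extracted to evaluate treatment engagement in the 6 months following integration". Their entry dates are not otherwise fixed.
- **Collection window (Measures, opening paragraph).** Engagement and abstinence data "will be collected monthly across 6 months prior to and post MBC integration". The anchor is the integration date, not the patient's induction.
- **Outcome.** The proportion of visits attended "out of total visits scheduled for each patient", "as well as the total number of weeks each patient was retained in treatment".
- **Unobserved months.** The only provision is an indicator that "urine drug screen data was unavailable for the months following patient treatment discontinuation". Nothing addresses time lost through late entry.
- **Eligibility (Phase 2, Participant selection).** Records qualify if patients "were inducted on medication for opioid use disorder within 6 months of MBC integration". Before or after is not stated.
- **Test (outcome data analysis).** T-tests "will be conducted to compare average pre- and post-MBC treatment engagement proportions/number of weeks of MOUD and counseling attended".

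**The concern.** The entry window and the follow-up window are the same interval. A patient who enters 26 weeks before integration can score up to 26 weeks; one who enters a week before can score at most one, even if never lost. With entry spread evenly, the average available follow-up is 13 weeks, not 26. Much of the variation in weeks retained then reflects entry date, and a t-test treats a patient still in treatment when the window closes as if that patient had dropped out.

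This is more than detail left to another document. The article itself states the sampling window, the collection window, the outcome and the test, and following all four as written gives the weaker analysis.

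The stakes go beyond the pilot. Under Sample size and power considerations, a small to medium effect on engagement or abstinence is part of the case for a larger trial, and the detected effect is to be used to calculate that trial's size. An effect shrunk by the measuring window could end a useful programme or inflate the next sample size.

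**Working it through.** **The plan's own figure, for scale.** With 80 charts per set, the detectable standardised difference is (z for alpha + z for power) × √(2/80).
- One-sided 5%, 80% power: (1.645 + 0.842) × 0.1581 = 0.393, which matches the stated 0.39.
- Two-sided 5%, 80% power: (1.960 + 0.842) × 0.1581 = 0.443.

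So 0.39 reproduces only as a one-sided figure, and the article does not state sidedness. Power below is two-sided 5% unless marked.

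**Inputs.** From the article: 80 charts per set; a 6-month window, taken as 26 weeks; retention of 51% to 63% at 3 to 6 months and as low as 43% at 6 to 12 months (introduction). Assumed: uniform entry over the window, exponential dropout, and the pre/post pairs of 6-month retention S shown below. The pair 51% v 72% was chosen because it gives an effect close to 0.39.

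**Formulas.** Dropout rate λ = −ln(S)/26.
- Mean weeks with a full 26 weeks from entry: (1 − S)/λ.
- Mean weeks inside the calendar window, uniform entry: (1/λ) × [1 − (1 − S)/(26λ)].
- SD from E[X²] = ∫ 2t·e^(−λt)·G(t) dt over 0 to 26, where G(t) is the share of patients with more than t weeks available (1 for full follow-up, 1 − t/26 for the window).
- d = difference in means / √[(SD₁² + SD₂²)/2]; power from the two-sample t-test with 80 per set.

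**Numbers in, 51% v 63%.** λ = 0.6733/26 = 0.025898 and 0.4620/26 = 0.017771.
- Full follow-up: 0.49/0.025898 = 18.92 and 0.37/0.017771 = 20.82 weeks; pooled SD 8.53; d = 1.90/8.53 = 0.22.
- Calendar window: 38.61 × (1 − 0.49/0.6733) = 10.51 and 56.27 × (1 − 0.37/0.4620) = 11.21 weeks; pooled SD 7.29; d = 0.70/7.29, or 0.095 before rounding.

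| Retention pre v post | Full 26 weeks: means, d, power | Calendar window: means, d, power |
|---|---|---|
| 51% v 63% | 18.9 v 20.8, 0.22, 29% | 10.5 v 11.2, 0.095, 9% |
| 51% v 72% | 18.9 v 22.2, 0.40, 71% | 10.5 v 11.7, 0.16, 17% |
| 43% v 60% | 17.6 v 20.4, 0.32, 52% | 10.0 v 11.0, 0.14, 15% |
| 63% v 75% | 20.8 v 22.6, 0.23, 31% | 11.2 v 11.8, 0.085, 8% |

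In the 51% v 72% row, one-sided power falls from 81% to 26%. In every row d falls by more than half.

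**No true effect (51% in both).** With the same uniform entry in both periods, both means are 10.51 and d = 0. With unequal entry:
- Post entry confined to the last 22 of 26 weeks: 9.18 v 10.51 weeks, d = −0.20, rejection 24%.
- Post entry confined to the first 22 weeks: 12.07 v 10.51 weeks, d = +0.22, rejection 29%.

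**Same charts, censored analysis.** A log-rank test with patients still in treatment at window end treated as censored has, by simulation, about 21% power against 9% for the t-test (51% v 63%), and about 52% against 17% (51% v 72%).

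**The case against.** Several points on the other side stand.

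- **No bias under equal entry.** If patients enter in the same pattern in both periods, truncation weakens the contrast but creates no false one. The article does not say that entry patterns differ; the 22-week cases are assumed and show sensitivity only.
- **Run-on into MBC.** A reader might infer that pre patients followed for six months from entry spend part of that time under MBC. Table 1, as extracted, places pre-MBC data extraction in Year 3, quarters 2 to 3, and the workshop in Year 4, quarters 3 to 4, and counselors start MBC only after the workshop. The schedule makes run-on unlikely, and it should not be claimed.
- **Attendance and urine results.** A reader might extend the cap to these. They are proportions, of visits scheduled and of screens in months present, so they are not mechanically truncated. They are affected only so far as attendance or abstinence changes with time since entry.
- **Survivors in the post set.** The eligibility wording does not say on which side of integration induction falls, so a reader might infer that long-stayers enter the post set. Measures calls the post charts new-patient charts, and the natural reading is new patients before and new patients after. This calls for a clarification and is not a demonstrated flaw.
- **Pilot status and small assumed effects.** The Discussion concedes limited power and the pre-post design, and 51% v 63% has only 29% power even with full follow-up. But the Discussion does not mention truncated follow-up, and the proportional loss is as large for an effect near the planned one.
- **A full protocol exists.** It may define the follow-up clock. The windows and test in the article nevertheless stand as stated.

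**Conclusion.** The point holds for weeks retained. As written, this component of the primary outcome is capped by entry date and then compared as a raw mean. With matching entry patterns the consequence is attenuation without bias: d falls by 55% to 64% across the four retention pairs, and for an effect near the planned 0.39 two-sided power falls from 71% to 17%. With unequal entry spread a false difference arises as well, |d| about 0.2 in the assumed 22-of-26-week cases.

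The sizes rest on uniform entry, exponential dropout and illustrative retention rates, none of which the article fixes as a planning assumption. They also take the post charts to be read to the end of the six months after integration. The direction of the attenuation does not depend on the exact values. It would not be right to say that the comparison is biased whatever happens.

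**What to change.** Change the Phase 2 wording before charts are drawn:

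1. Start each patient's clock at induction.
2. State that pre charts are inducted before, and post charts on or after, the site's first MBC delivery.
3. Analyse retention as time to discontinuation, censored at the end of each window, by log-rank or by restricted mean weeks to a common horizon, in place of the t-test on raw weeks.

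An alternative to step 3 is the same follow-up length from entry for both sets, with the pre intake closing early enough that follow-up ends before MBC begins. This would also equalise follow-up for attendance and urine proportions, which is a secondary gain.

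**Cost.** The censored analysis uses the same charts, needs induction and last-visit dates from them, and is slightly more complex to run and report. The alternative narrows the intake period or shortens the horizon, and a short horizon has its own price: a fixed 13 weeks at 51% v 63% gives d of about 0.17 and about 18% power, below the roughly 21% of the censored log-rank. Neither option rescues a small effect with 80 charts per set; they stop the window from removing most of what can be seen.

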**Methods:**

This study will be conducted in two phases. Phase 1 will include RAPICE site visits, qualitative interviews (*N* = 32–48 total), and quantitative surveys (*N* = 64–80 total) with staff at eight programs to build community partnerships and evaluate contextual factors impacting MBC implementation. Mixed methods data will be analyzed using immersion/crystallization and thematic analysis to inform MBC adaptation and site selection. Four programs selected for Phase 2 will participate in MBC electronic medical record integration, training, and ongoing support. Chart reviews will be completed in the 6 months prior-to and following MBC integration (*N* = 160 charts, 80 pre and post) to evaluate effectiveness (patient opioid abstinence and treatment engagement) and implementation outcomes (counselor MBC exposure and fidelity).

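### Weeks retained is read inside the same 6-month block in which patients enter, and a t-test on raw weeks treats stays cut off by the block as complete

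*Protocol article*

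**What the plan says.** All references are to Phase 2 of the protocol article.

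- **Who is sampled.** Participant selection admits records of patients who "were inducted on medication for opioid use disorder within 6 months of MBC integration". Under Measures, about 20 pre-MBC charts per site are "randomly selected from new patients that entered treatment over the 6 months prior to MBC integration". A separate set of about 20 new-patient charts per site "will be extracted to evaluate treatment engagement in the 6 months following integration".
- **When outcomes are read.** Measures states: "Patient treatment engagement data and opioid abstinence will be collected monthly across 6 months prior to and post MBC integration". The Methods part of the abstract gives the same window: "Chart reviews will be completed in the 6 months prior-to and following MBC integration".
- **What is measured.** Engagement is the share of each patient's scheduled visits that were attended, "as well as the total number of weeks each patient was retained in treatment". The secondary outcome is the proportion of negative opioid urine screens. Its missing-data indicator covers only the months after a patient has left treatment.
- **How it is analysed.** The outcome data analysis section uses t-tests to "compare average pre- and post-MBC treatment engagement proportions/number of weeks of MOUD and counseling attended".
- **What hangs on it.** Under Sample size and power considerations, 80 charts per period are said to be powered for an effect of 0.39. A small to medium effect on engagement or abstinence, together with Phase 1 acceptability and feasibility, supports a larger trial. The observed effect is also used to size that trial.

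**The concern.** The entry window and the outcome window are the same calendar block, both fixed to integration. A patient who enters in week w of the block can show at most 26 − w weeks. Anyone still in treatment at the end of the block has a stay that is cut off, at a ceiling that differs from patient to patient. A t-test on raw weeks takes those cut-off values as finished stays.

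Two consequences follow. Entry date adds variation to weeks that has nothing to do with MBC, and late entrants have too little time for a retention gain to show, so a real effect shrinks. If patients in one period happen to enter earlier on average than in the other, a difference also appears without any MBC effect. Weeks retained feeds the effect size that informs the next trial, so a true gain of the size the study was planned around could be read as small or absent.

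**Working it through.** **1. The plan's own figure.** For a two-sample t-test with 80 per group, 5% alpha and 80% power, the detectable d is 0.395 one-sided (0.393 by the normal approximation) and 0.446 two-sided. The stated 0.39 therefore matches a one-sided test, although the article gives neither sidedness nor power. At d = 0.39, power is 0.79 one-sided and 0.69 two-sided. I carry both.

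**2. Assumptions (not in the article).** The block is 26 weeks and entry is uniform over it. Drop-out follows a Weibull curve with shape 0.6 (early-peaking), 1.0 (exponential) or 1.5. Pre-MBC retention at 26 weeks is 43%, 51% or 63%, taken from the retention figures in the introduction. Post-MBC retention is set so that d = 0.39 when everyone is followed for 26 weeks from entry.

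**3. Formulas.** Let S(t) be the retention curve and C the available weeks, uniform on 0 to 26.

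- Mean weeks, full follow-up: m = ∫₀²⁶ S(t) dt
- Mean weeks, calendar block: ∫₀²⁶ S(t)(1 − t/26) dt
- Share cut off while still in treatment: m/26
- Entry-date share of variance: Var(E[weeks | C]) / Var(weeks)

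**4. Central case (exponential, 51% pre).** For the exponential the block mean is (1/λ)(1 − m/26).

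- Pre: λ = −ln(0.51)/26 = 0.0259, so 1/λ = 38.61. m = 0.49 × 38.61 = 18.92. Block mean = 38.61 × (1 − 18.92/26) = 10.51. Cut off: 18.92/26 = 73%.
- Post (71.6% retained): 1/λ = 77.83. m = 0.284 × 77.83 = 22.10. Block mean = 77.83 × (1 − 22.10/26) = 11.67. Cut off: 85%.
- Difference: 3.18 weeks with full follow-up and 1.15 weeks in the block (unrounded means), a loss of 64%.
- Block SDs are 7.23 and 7.42 (pooled 7.33), so d = 1.15/7.33 = 0.157.
- Power falls from 0.69 to 0.17 two-sided and from 0.79 to 0.26 one-sided. Recovering it would take about (0.39/0.157)² ≈ 6 times the charts.

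**5. All nine scenarios.**

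| Shape | Pre → post retained | Pre cut off | Weeks difference lost | Entry-date share of variance (pre) | Block d | Power, 2-sided | Power, 1-sided |
|---|---|---|---|---|---|---|---|
| 0.6 | 43 → 63% | 60% | 58% | 36% | 0.22 | 0.28 | 0.39 |
| 0.6 | 51 → 71% | 67% | 59% | 43% | 0.20 | 0.24 | 0.35 |
| 0.6 | 63 → 82% | 75% | 60% | 54% | 0.17 | 0.19 | 0.29 |
| 1.0 | 43 → 64% | 68% | 63% | 50% | 0.17 | 0.19 | 0.29 |
| 1.0 | 51 → 72% | 73% | 64% | 57% | 0.16 | 0.17 | 0.26 |
| 1.0 | 63 → 82% | 80% | 65% | 67% | 0.13 | 0.13 | 0.21 |
| 1.5 | 43 → 65% | 74% | 68% | 65% | 0.13 | 0.13 | 0.20 |
| 1.5 | 51 → 72% | 78% | 69% | 70% | 0.12 | 0.11 | 0.18 |
| 1.5 | 63 → 83% | 84% | 70% | 78% | 0.10 | 0.09 | 0.15 |

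**6. Same charts, censored analysis.** In the central case about 34 discontinuations are seen within the blocks. The hazard ratio is ln(0.716)/ln(0.51) = 0.50. Log-rank power is about Φ(0.70 × √(34/4) − 1.96) ≈ 0.53; simulation gave 0.51. That compares with 0.17 for the t-test on the same data.

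**7. Unequal entry.** With no MBC effect in the central case, entry averaging 2 weeks earlier in one period gives d of about 0.22, and 4 weeks earlier gives about 0.43. These shifts are illustrative.

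**8. The proportions.** With even entry, and ignoring drop-out, treatment months 1 to 6 are observable in the ratio 6:5:4:3:2:1. Months 1–2 supply 11/21 = 52% of patient-months, against 2/6 = 33% with equal follow-up. In an illustrative simulation, entry date explained about 0% of the variance of the attendance proportion and about 1% of that of the abstinence proportion.

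**The case against.** **The article is condensed and does not say that a chart stops at the end of the block.** That is so, and the full protocol could define an index date. But the sampling window, the outcome window, the measure and the test are all stated, and as stated they do not fit together. Nothing in the text points to follow-up from each patient's own entry.

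**Weeks is only one part of the outcome.** This stands. Visit attendance is the other part, and a signal on abstinence could also support a larger trial. Diluted weeks alone would not decide the matter, and the article already concedes limited power. It does not mention this source of power loss, which can be avoided.

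Four stronger readings are tempting, and the documents do not support them:

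- A reader might infer that the monthly attendance and abstinence results are also mainly a product of entry date. They are not: each is a proportion on the patient's own denominator. Early treatment months are over-represented, and that is all.
- A reader might infer that entry date always accounts for most of the variation in weeks. It accounts for 36% to 78%, and for less than half when drop-out peaks early and retention is 43% or 51%.
- A reader might infer that pre-MBC patients run on into MBC exposure. Table 1, as far as its layout can be read, places the first outcome extraction before the integration meetings. MBC integration has counselors starting MBC only after the workshop.
- A reader might infer that the design manufactures benefit. With similar entry patterns it dilutes; bias needs patterns that differ.

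**Conclusion.** The point holds for weeks retained. Read as written, the plan compares stays of which 60% to 84% in the pre period are cut off by the calendar, as though they were complete. Across the nine scenarios, 58% to 70% of the true difference in weeks is lost. The standardized difference loses 44% to 75% of its size, and more than half in seven of the nine. The direction is robust to the shape of drop-out and the level of retention. The exact size rests on uniform entry, a 26-week block and the assumed retention curves, none of which the article gives. The consequence is an understated retention effect and lost power. Bias in either direction is possible if entry patterns differ, because the plan neither balances nor adjusts for them.

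**What to change.** 1. Add two fields to the extraction, both as week offsets from integration so that the data stay de-identified: induction and last attended visit.
2. Define weeks retained as time from each patient's own induction to discontinuation. Censor patients still in treatment at the end of the block and, for pre-MBC patients, no later than the start of MBC.
3. Replace the t-test on raw weeks with Kaplan–Meier curves and a log-rank or Cox comparison, or with restricted mean weeks to a common horizon that the data support, for example 13 weeks.
4. Take the retention effect size for planning the larger trial from that analysis.
5. Report the distribution of entry dates in each period, and state that the attendance and abstinence proportions weight early treatment months more heavily.

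**Cost.** Two fields and a change of wording, with no extra charts. The downside is a shorter common horizon, or less precision at late weeks.

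**Optional.** Giving every pre-MBC patient a full 26 weeks before integration would require changing the rule that induction falls within 6 months of integration. It would also move the two cohorts further apart in time. That is a design choice and is not needed for this repair.

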**Supplementary Information:**

The online version contains supplementary material available at 10.1186/s13722-022-00327-0.

Opioid overdoses are a public health emergency in the United States (US). In 2019, approximately 70% of prescription drug overdose deaths in the U.S. involved opioids [1]; preliminary data suggest that overdose rates have continued to rise during the COVID pandemic [2, 3]. To address this urgent public health issue, the gold standard, first-line evidence-based intervention is medication for opioid use disorder (MOUD), most commonly with methadone or buprenorphine [4–6]. MOUD is effective for reducing opioid use, improving treatment retention (when compared to placebo/no medication), and reducing the risk of overdose [4, 6]. However, MOUD is not sufficient for many patients, and treatment retention remains a challenge [7–10]. A meta-analysis of 18 randomized controlled trials revealed that only 51% to 63% of patients initiated on medication fully engage and remain in treatment for 3 to 6 months [7]. These retention numbers become as low as 43% across 6 to 12 months [7]. Such low retention rates increase the risk of lethal opioid overdose and heighten the need for evidence-based adjunctive psychosocial interventions [11].

Unfortunately, the uptake of adjunctive psychosocial interventions in opioid treatment programs (OTPs) that dispense methadone and buprenorphine has been extremely low [12, 13]. Counselors in OTPs have reported a myriad of challenges to implementing evidence-based manualized psychosocial interventions such as contingency management and cognitive behavioral therapy, including: limited time/resources to learn new models, lack of alignment with existing theoretical orientations, disagreements in the field regarding intensity and type of intervention, incompatibility with group therapy as a primary OTP treatment model, and beliefs that manualized interventions are too “rigid” or “inflexible” [14–17]. Thus, there is an unaddressed need for adjunctive psychosocial interventions that can be flexibly applied by OTP counselors in a group therapy format, delivered by counselors with an array of theoretical orientations, and scaled to accommodate the typical workflow in community-based OTPs.

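### The in-program abstinence score depends on retention, which MBC is meant to raise; compared by month it can move against MBC when drug use is unchanged

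*Protocol article*

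**What the plan says.** Under Phase 2, Measures, opioid abstinence is the secondary effectiveness outcome: the proportion of negative opioid urine screens, collected for each patient by month. The protocol expects some patients to discontinue and gives them a rule: "opioid abstinence will be calculated as the proportion of negative urine screens for each month that they were present in the program". Later months are only flagged: "We will include an indicator in the data set to denote that urine drug screen data was unavailable for the months following patient treatment discontinuation".

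The primary effectiveness outcome, treatment engagement, is the proportion of visits attended "out of total visits scheduled for each patient, as well as the total number of weeks each patient was retained in treatment". The aims hypothesise that both engagement and negative screens will increase after MBC integration.

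The section on outcome data analysis compares average pre and post abstinence proportions by t-test. It does not say whether the observation is a patient or a patient-month. Under Sample size and power considerations, a small to medium effect on either engagement or abstinence, together with Phase 1 acceptability and feasibility evidence, would be preliminary support for a larger trial.

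The introduction shows how common leaving is in published trials: "only 51% to 63% of patients initiated on medication fully engage and remain in treatment for 3 to 6 months", and "These retention numbers become as low as 43% across 6 to 12 months".

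**The concern.** The denominator of the abstinence score ends when the patient leaves. A patient with one clean month who then drops out scores 100%, as does a patient who is clean for six months. Time in the program is something MBC is hypothesised to lengthen, so the score conditions on a variable that the intervention may affect.

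If patients who would otherwise have left are more often using, keeping them adds positive screens to the post-integration months. The abstinence comparison can then worsen although nobody's drug use has changed, or hide a true benefit. What is at stake is the answer to the abstinence hypothesis and, through the either-outcome criterion, the decision on a larger trial.

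**Working it through.** **Inputs from the protocol.** 80 charts before and 80 separate charts after integration; a detectable effect of 0.39; background retention of 51% to 63% at 3 to 6 months. The protocol gives no abstinence rates, screening frequency or expected effect of MBC on retention. Those are my assumptions below.

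**Yardstick.** (1.645 + 0.842) × √(2/80) = 2.487 × 0.158 = 0.393, so 0.39 is reproduced with a one-sided 5% test and 80% power. A two-sided 5% test gives about 0.44. The protocol states none of these settings, and 0.39 serves here only as a scale.

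**Step 1: two types of patient, by hand.** Assume 80% negative screens in patients who would stay anyway and 40% in all others. Leavers stay one month, retention rises from 51% to 63%, and nobody's drug use changes.

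- Month 6, those present: before 80.0%; after (0.51 × 80 + 0.12 × 40)/0.63 = 72.4%. Difference -7.6 points.
- Pooled patient-months: before (0.51 × 6 × 80 + 0.49 × 40)/(3.06 + 0.49) = 264.4/3.55 = 74.5%; after (244.8 + 0.12 × 6 × 40 + 0.37 × 40)/(3.06 + 0.72 + 0.37) = 288.4/4.15 = 69.5%. Difference -5.0.
- One proportion per patient: 0.51 × 80 + 0.49 × 40 = 60.4% in both periods. Difference 0.0.
- Fixed six-month denominator, months after leaving counted as not negative: before 40.8 + 0.49 × 40/6 = 44.1%; after 40.8 + 4.8 + 0.37 × 40/6 = 48.1%. Difference +4.0.

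Add a true benefit of 3 points in every patient. The differences become -4.6 (month 6), -2.0 (pooled), +3.0 (per patient) and +6.1 (fixed), so the first two have the wrong sign. If instead everyone has 60% negative screens, all three in-program differences are zero.

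**Step 2: drug use that changes over time.** Assume 35% using at entry, 12% monthly relapse, and 85% or 30% negative screens when abstinent or using. Assume four screens a month (24 planned) and monthly dropout of 4% when abstinent. Among patients who are using, monthly dropout falls from 25% to 12%; nothing else changes. Screens in a month precede leaving. Calculated exactly, month by month:

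| Measure | Before | After | Difference (points) |
|---|---|---|---|
| Retained at end of month 6 | 44.5% | 61.3% | +16.8 |
| Negative at month 6, those present | 59.9% | 52.9% | -7.0 |
| Negative, average over the six months, those present | 62.4% | 58.7% | -3.7 |
| Mean of one proportion per patient | 58.6% | 58.0% | -0.6 |
| Negative over all 24 planned screens | 46.7% | 49.4% | +2.7 |

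The true percent negative over six months, counting time after leaving, is 0.30 + 0.55 × 0.65 × (1 - 0.88^6)/(6 × 0.12) = 56.6% in both periods. The per-patient shift is -0.6/27.0, or d of about -0.02. The fixed-window shift is +2.7/30.7, or d of about +0.09.

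Timing matters somewhat. If patients leave before each month's screens, and those with no screen are left out, the per-patient mean goes from 62.7% to 59.5%. That is -3.2/26.9, or d of about -0.12.

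**Step 3: a second model.** Let abstinence and leaving share a continuous patient propensity, with retention rising from about 56% to 69% and no true effect. The per-patient mean then shifts by about 0 to -1.3 points, pooled months by -1.4 to -2.6, month 6 by -3.1 to -5.2, and the fixed-window measure by +2.4 to +4.0.

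**The case against.** The strongest reply is that the natural reading has little bias. Abstinence is scored for each patient, and t-tests on 80 against 80 charts suggest one value per patient. On that reading the distortion is between 0 and about 3 points, d no larger than about 0.12 against the planned 0.39. This stands, and it limits the point. But the same section collects the proportion monthly and the analysis section does not name the unit, so the vulnerable comparisons are not ruled out.

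A second reply is that a fixed window is not an unbiased replacement: in Step 2 it rises by 2.7 points although drug use is unchanged. This also stands. It measures documented abstinence, a different quantity, so making it the main measure would be a choice to justify. Reporting both needs no such choice.

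A reader might infer four stronger claims, which the protocol does not support:

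- *That attendance is also scored only over time in the program.* The denominator is "out of total visits scheduled for each patient". Whether visits after discontinuation count is left open.
- *That the engagement hypothesis could be answered in the wrong direction.* Weeks retained is part of the engagement outcome and is compared directly, so an early leaver scores few weeks. No calculation here shows a reversal for engagement.
- *That any effect on retention biases both outcomes.* Bias in the in-program score needs leaving to be related to drug use, or abstinence to change within patients. Without either it is zero.
- *That imputation will fill in screens after discontinuation.* The sentence "analyses will employ multiple imputation methods in the event of substantial missing data" is general, and the months after leaving have their own rule.

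**Conclusion.** The point holds for opioid abstinence, the secondary effectiveness outcome. The in-program proportion is conditional on retention. If patients kept longer are more often using, it is biased against MBC: by about 4 to 7 points for monthly comparisons in the main illustration (Step 2), enough in Step 1 to reverse the sign of a true 3-point benefit. With one proportion per patient the shift in the main illustration is about -0.6 points, and no more than about -3 in the variants tried.

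These sizes rest on assumed abstinence, relapse and dropout rates and on an assumed effect of MBC on retention; the protocol gives none for this trial. That the score is conditional on staying does not depend on them. The point should be settled before Phase 2 analysis because abstinence alone, with the Phase 1 evidence, can meet the criterion for a larger trial. It does not undermine the primary outcome.

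**What to change.** 1. In the abstinence definition and the outcome data analysis section, state that the t-test uses one value per patient, not patient-months or a single late month.
2. Beside the in-program proportion, report a fixed six-month measure counted from induction: documented negative screens (or months) divided by those planned, with months after discontinuation counted as not documented abstinent.
3. When applying the criterion under Sample size and power considerations, read both abstinence measures together with weeks retained.

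The cost is a few sentences and a few lines of code. The monthly screens and the discontinuation indicator are already to be extracted; the months version needs no further data, while the screens version needs the planned number of screens. Charts are drawn from patients who enter during each six-month period, so some six-month windows will run past the period's end. The text should say how these are handled, because the end of data collection is not discontinuation. The downside is that the fixed-window measure partly reflects retention, so neither measure should be read alone.
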